## Abstract

**Background:**

Heart failure (HF) is a major chronic illness and results in high morbidity and mortality. The most frequent cause of HF with reduced ejection fraction (HFREF) is coronary artery disease (CAD). Although revascularisation of ischemic myocardium lead to improvements in myocardial contractility and systolic function, it cannnot restore the viability of the already necrotic myocardium.

**Methods/design:**

The aim of our prospective randomised study is to assess the efficacy of the retrograde application of non-selected bone marrow autologous cells concentrate (BMAC) in patients with HFREF of ischemic aetiology. The evaluated preparation is concentrated BMAC, obtained using *Harvest SmartPReP2* (Harvest Technologies, Plymouth, MA, USA). The study population will be a total of 40 patients with established CAD, systolic dysfunction with LV EF of ≤40% and HF in the NYHA class 3. Patients have been on standard HF therapy for 3 months and in a stabilised state for at least 1 month, before enrolling in the clinical study. Patients will be randomised 1:1 to either retrograde BMAC administration via coronary sinus or standard HF therapy. The primary end-points (left ventricular end-systolic and end-diastolic diameters [LVESd/EDd] and volumes [LVESV/EDV] and left ventricular ejection fraction [LV EF]) will be assessed by magnetic resonance imaging. The follow-up period will be 12 month.

**Discussion:**

The application of bone marrow stem cells into affected areas of the myocardium seems to be a promising treatment of ischemic cardiomyopathy.

The Harvest BMAC contains the entire population of nuclear cells from bone marrow aspirates together with platelets. The presence of both platelets and additional granulocytes can have a positive effect on the neovascularisation potential of the resulting concentrate. Our assumption is that retrograde administration on non-selected BMAC via coronary sinus, due to the content of platelets and growth factors, might improve left ventricular function and parameters compared to standard HF therapy. Furthermore, it will be associated with improved exercise tolerance in the six-minute corridor walk test and an improvement in the life quality of patients without increasing the incidence of severe ventricular arrythmias.

**Trial registration:**

(ClinicalTrials.gov; https://clinicaltrials.gov; NCT03372954).

## Background

Heart failure (HF) is a major chronic illness and results in high morbidity and mortality; for instance, the mean mortality rate of severe heart failure in the NYHA IV class is 40–50% per year [1]. The most frequent cause of left ventricular systolic dysfunction and the development of HF with reduced ejection fraction (HFREF) in developed countries is coronary artery disease (CAD). Although percutaneous coronary angioplasty and surgical revascularisation of ischemic myocardium lead to improvements in angina pectoris, myocardial contractility and systolic function, none of these methods can restore the viability of the already necrotic myocardium [1].

Substitution of impaired myocytes in affected areas of the myocardium could stimulate cardiomyocytes regeneration, support the neovascularisation and thus prevent remodelling of the left ventricle. Primary pluripotent progenitor cells in bone marrow are able to disperse into functional vascular tissue, which has led to great interest in their use in the treatment of acute myocardial infarction (MI), left ventricular systolic dysfunction and HF [2].

As preclinical data prove, bone marrow autologous cells concentrate (BMAC) are able to separate in vascular structures and with the aid of paracrine mechanisms can improve the function of existing cardiomyocytes or angiogenesis [2, 3]. Studies have already shown that the administration of BMAC leads to improved myocardial perfusion and left ventricular function with minimal adverse effects, and it is therefore safe and offers potential clinical benefits [4] and contrary to skeletal myoblasts, there is no evidence of increase in malignant arrhythmias [1–3].

### Aim

The aim of this prospective randomised study is to assess the efficacy of the retrograde application of non-selected BMAC in patients with HFREF of ischemic aetiology. The evaluated preparation is concentrated BMAC, obtained using *Harvest SmartPReP2* (Harvest Technologies, Plymouth, MA, USA).

Our assumption is that non-selected BMAC administrations will lead to improvements in the left ventricular ejection fraction (LV EF), the left ventricular end-systolic and end-diastolic diameters and volumes (LVESd/EDd and LVESV/EDV) compared to standard HF therapy. Furthermore, it will be associated with improved exercise tolerance in the six-minute corridor walk test, a decrease in NYHA and CCS classes and an improvement in the life quality (QoL) of patients. At the same time, this therapy will not increase the incidence of severe ventricular arrythmias detected by 24-h ECG Holter monitoring.

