## Methods/design

The study population will be a total of 40 patients with established CAD and left ventricular systolic dysfunction with an EF of ≤40% and HF in the NYHA class 3. CAD will be demonstrated based on previous coronary angiography (myocardial infarction > 6 months, presence of significant coronary stenosis, previosu revascularisation) or Tc SPECT (perfusion defects). The patient follow-up duration will be 12 months.

Patients have been on standard HF therapy for 3 months and in a stabilised state for at least 1 month, before enrolling in the clinical study. A list of inclusion and exclusion criteria is provided in Table 1.

**Table 1 Tab1:** Inclusion and exclusion criteria

Inclusion criteria:	
• Patients with chronic heart failure and left ventricular ejection fraction ≤40% with coronary artery disease and with symptoms of heart failure in the NYHA class 3 on standard heart failure therapy for 3 months and in a stabilised state for at least 1 month,	
• Age 40–80 years	
• Informed, written consent by the patient	
• Ability to comply fully with the study protocol	
• Negative pregnancy test (and effective contraception) in women with childbearing potential	
Exclusion criteria:	
• Previous bone marrow disease (especially myelodysplastic syndrome or non-Hodgkin’s lymphoma)	
• Repeated acute coronary syndrome <1 month	
• CRT device with LV lead in CS	
• Active infection or ATB treatment <1 week	
• Previous malignant ventricular arrhythmias without ICD implantation	
• Anemia (HTC ≤ 28%), leukocytosis (≥14.000/mm^3^) or thrombocytopenia (≤50.000/mm^3^)	
• Previous bleeding diathesis	
• Need for hematopoietic growth factor treatment (e.g. erythropoetin, G-CSF)	
• Impossibility of aspiration 240 ml of bone marrow	
• Hepathopathy or cirrhosis (bilirubin, ALT or AST ≥2,5x ULN)	
• Chronic kidney disease >3b stage (eGFR <45 ml/min/1.73m^2^)	
• Uncontrolled hypertension	
• Need for high dose (> 7.5 mg/day) corticotherapy within the next 6 months	
• Inability to stop anticoagulation therapy (> 72 h) before bone marrow aspiration	
• Known malignancies requiring actino or chemotherapy, or previous actinotherapy	
• Patients with a BMI > 40	
• Known allergy to contrast agents	
• Other comorbidities with a life expectancy of 6 months	

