Patients will be randomised 1:1 to one of the following treatment methods: either retrograde BMAC administration via coronary sinus or the control group with standard HF therapy. Patients randomised to the control group will not undergo bone marrow collection, due to ethical reasons. Only standard right heart catheterisation will be performed as sham procedure.

The primary objectives of the clinical study are to improve the LV EF and reduce the LVESd/EDd and LVESV/EDV assessed by magnetic resonance imaging (MRI), and to improve exercise tolerance in the six-minute corridor walk test.

The secondary objectives include identifying the occurrence of severe ventricular arrhythmias according to 24-h ECG Holter monitoring, improving on the NYHA and CCS classes, reducing hospitalisations due to decompenzation of HF, assessing the impact on QoL of patients using the Kanas City Cardiomyopathy Questionare (KCCQ-12) and ensuring the safety of BMAC retrograde administration via coronary sinus by evaluating all adverse events (AE).

All patients will continue on the standard HF treatment during the clinical follow-up (ACE inhibitor/ATII blockers, beta-blockers, MRA, diuretics) and medication necessary for secondary CAD prevention (ASA/clopidogrel, statins). The monitored parameters will be measured echocardiographically in ICD-implanted patients not able to undergo MRI. Patient with cardiac resynchronization therapy (CRT) device (or CRT-ICD) with LV lead placed in CS will not be included. We also not include patients with known contrast allergy.

Written informed consent was obtained from each patient before enrollment in the study. The study protocol complied with the Declaration of Helsinki and was approved by the Ethics Committee of University Hospital Ostrava, Czech Republic. The study was registered at ClinicalTrials.gov (https://clinicaltrials.gov; NCT03372954).

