### Further follow-up

The follow-up visits will be performed according to the protocol after 1, 3, 6 and 12 months (Visits 3, 4, 5 and 6) **[**Table 2**]**, and a physical examination as well as 12 lead ECG and laboratory tests (blood count + diff, clinical biochemistry, troponin I and NT-pro-BNP) will be performed during each visit and any AEs (cardiovascular death, hospitalisation due to decompensation of HF, acute MI, etc.) recorded. An echocardiographic examination will be performed during screening, and MRI examinations will take place on enrolment (Visit 1) and on the final Visit 6 in month 12. LV parameters and a percentage of total myocardial scar (TMS%) and peri-infarct border zone (PI%; PI = 2–3 SD) will be measured using delated myocardial enhancement assessment [5].

In addition, 24-h Holter ECG monitoring will be performed on enrolment (Visit 1) and after 1 month (Visit 3). Exercise tolerance using a six-minute corridor walk test and QoL (KCCQ-12) will be monitored prior to enrolment (Visit 1) and after 6 (Visit 5) and 12 months (Visit 6) **[**Table 2].

Interventional cardiologists will not be blinded to the assigned therapy, but clinical evaluation, measurement of MRI parameters and data processing will be performed by blinded, independent persons.

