### Sample size and statistical analysis

The statistical estimate of the size of the file was based on the data from previous studies in patients with congestive heart failure [6] in which was reached the difference of 13.0 + 12.9 ml in LVESV between study and control groups. α type I error of 5%, and β test strength of 80% were used to determine the required group size of 17 patients per group. When including an expected loss of 10% of patients in the 12-month follow-up (including MRI drop out), the resulting size of our group was 40 patients (20 per arm).

Continuous variables with normal distribution will be presented as mean and standard deviation (SD) and will be compared using Student 2-sample *t* test. Continuous variables with non-normal distribution will be presented as the median and range (minimum–maximum or lower and higher percentile) and will be compared using the nonparametric Mann–Whitney *U* test. Categorical variables will be presented as counts and percentages and will be compared using the χ2 or Fisher exact test. Odds ratios (OR) are expressed with 95% CI. A *p* < 0.05 will be considered significant. All statistical analyses will be performed using IBM SPSS Statistics version 22.

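### The hypothesis that BMAC does not increase severe ventricular arrhythmias cannot be supported by a difference test on one post-treatment Holter in 20 patients per arm

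*Protocol article*

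**What the plan says.** The Aim section states, within a paragraph introduced as the authors' assumption, that "this therapy will not increase the incidence of severe ventricular arrythmias detected by 24-h ECG Holter monitoring". The abstract's Discussion makes the same prediction: benefit "without increasing the incidence of severe ventricular arrythmias".

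The secondary objective in Methods/design is worded differently and descriptively: "identifying the occurrence of severe ventricular arrhythmias according to 24-h ECG Holter monitoring". Evaluation of all adverse events is listed there as a further secondary objective.

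On timing, Further follow-up says that "24-h Holter ECG monitoring will be performed on enrolment (Visit 1) and after 1 month (Visit 3"), and Table 2 agrees. There is therefore one Holter recording after treatment, although "The patient follow-up duration will be 12 months". Visit ECGs and adverse events are recorded at months 1, 3, 6 and 12, and patients have at least 24 hours of ECG monitoring in hospital after the procedure.

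On analysis, Sample size and statistical analysis says: "Categorical variables will be presented as counts and percentages and will be compared using the χ2 or Fisher exact test". Odds ratios are to carry 95% confidence intervals, and a p-value below "0.05 will be considered significant". The sample size of 40 is derived from LVESV alone.

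**The concern.** The prediction and the stated comparison do not match. A test of difference can reject equality, but failing to reject it is not evidence that an increase is absent. To support a statement of no increase, one must name an excess that matters and show that the confidence interval excludes it. The article names no such excess and gives no arrhythmia rate, and its sample size was set for a continuous imaging outcome.

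A safety statement is at stake for an invasive cell therapy in NYHA class 3 patients with an ejection fraction of 40% or less. The Background itself raises malignant arrhythmia as a concern with another cell type. The prediction is also confined to one 24-hour window at month 1, while the trial collects arrhythmia-relevant data for a year.

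**Working it through.** **Inputs from the article.** 20 patients per arm (17 per arm was the required evaluable number), 1:1 allocation, χ2 or Fisher test, significance level 0.05 (sidedness is not stated; two-sided is assumed).

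**Inputs assumed.** All arrhythmia rates and margins below are assumptions, because the article gives none. They are shown as a range.

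**Step 1: the article's own sample size.** Read 13.0 ml as the LVESV difference and 12.9 ml as the SD, with two-sided 5% and 80% power. The noncentral-t calculation gives 78.8% power at 16 per arm and 81.3% at 17, so 17 per group is reproduced. Allowing for 10% loss, 17/0.9 = 18.9, which rounds up to 19 per arm or 38 in total; the article uses 40. This calculation is sound for LVESV but does not concern arrhythmia.

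**Step 2: power to detect harm.** Exact power of the two-sided Fisher test is the sum of Bin(i; n, p_BMAC) × Bin(j; n, p_control) over all tables with i > j and p < 0.05.

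| Assumed control vs BMAC rate | Fisher, n=20 per arm | Fisher, n=17 per arm | χ2 approximation, n=20 per arm |
|---|---|---|---|
| 5% vs 10% | 1.6% | 1.0% | 8.6% |
| 10% vs 20% | 7.2% | 5.3% | 13.9% |
| 5% vs 20% | 16.8% | 11.6% | 29.5% |
| 10% vs 30% | 24.2% | 18.6% | 34.8% |
| 5% vs 30% | 44.6% | 34.7% | 55.1% |

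**Step 3: what would count as significant.** With no control events, the two-sided Fisher p-value for x BMAC events is 2 × C(20,x)/C(40,x).
- 4 vs 0: 2 × 4845/91390 = 0.106.
- 5 vs 0: 2 × 15504/658008 = 0.047.

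So at least 5 vs 0 is needed; with one or two control events the thresholds are 7 vs 1 and 9 vs 2.

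**Step 4: what a reassuring result would leave open.** The Wilson upper limit for 0/20 is z²/(n + z²) = 3.84/23.84 = 0.161. With 0 events in both arms, the Newcombe upper 95% limit for the risk difference is therefore +16 percentage points. It is +19 points at 1 vs 1 and +21 points at 2 vs 2. The Clopper–Pearson upper limit for BMAC incidence at 0/20 is 1 − 0.025^(1/20) = 16.8%.

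**Step 5: the odds-ratio interval.** The sample odds ratio is 0/0 when neither arm has an event, and zero or infinite when only one arm has none. With few events these are plausible outcomes.

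**Step 6: what a no-increase claim would need.** For non-inferiority with equal true rates p, margin m, one-sided 0.025 and 80% power, n per arm = (1.96 + 0.84)² × 2p(1 − p)/m².
- p = 5%: 299 for a 5-point margin, 75 for 10 points, 19 for 20 points.
- p = 10%: 566, 142 and 36 for the same margins.

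In these scenarios, 20 per arm is enough only for a 20-point margin at a rate of about 5%.

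**The case against.** The strongest reply is that the article never commits the error. The sentence in the Aim is presented as an assumption, and the formal secondary objective only asks for occurrence to be identified. Nowhere does the text say that a non-significant result will be taken as no increase. A reader might infer that rule because no other criterion is given, but the document does not state it. That stands, and the point is worded accordingly.

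A reader might also infer that the trial would almost always report arrhythmic safety however large the harm. That goes too far: with 20 per arm, Fisher power is 45% for 5% vs 30% and 72% for 5% vs 40%. The weakness is severe for a doubling to quadrupling of low rates, less so for very large increases. The result can also depend on the test chosen: 4/20 vs 0/20 gives p=0.106 by Fisher but 0.035 by uncorrected χ2. Fisher is the usual choice here because only two events per arm are expected.

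It is fair, too, that safety is not monitored by one Holter alone, since adverse events, visit ECGs and post-procedure monitoring are planned. Only the stated hypothesis is tied to Holter. The planned odds ratios with 95% CI do provide an interval, but no limit is named for it to exclude.

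Finally, a margin or interpretation rule may be in the full protocol or analysis plan, which is not shown. Its absence here is therefore not counted as a fault. No such rule, however, would let 20 per arm support the prediction unless a very large excess were accepted.

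**Conclusion.** The point holds as an inconsistency between a stated hypothesis and the stated means of examining it. A non-significant χ2 or Fisher result from a single month-1 Holter in 20 per arm could not support a conclusion of no increase. Under assumed rates from 5% vs 10% up to 10% vs 30%, Fisher would miss the increase in about 76% to 98% of trials (1 − 0.242 and 1 − 0.016). Even an event-free trial would be compatible with an excess of about 16 percentage points. The power figures rest on assumed rates and a two-sided 5% level. The 16-point limit needs no assumed rate but takes all 20 patients per arm as evaluable; with fewer it is wider. The LVESV sample size is not at fault. This is a cheap and worthwhile correction, not a flaw in the trial's primary comparison.

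**What to change.** 1. Reword the prediction in the abstract and the Aim so that it matches the descriptive secondary objective in Methods/design.
2. For severe ventricular arrhythmia, report counts and incidence per arm and the risk difference with a 95% CI suited to sparse counts (for example Newcombe). State that a non-significant p-value will not be taken as absence of an increase.
3. Keep the month-1 Holter result as planned. Alongside it, report severe ventricular arrhythmia over the full 12 months from the adverse-event records and visit ECGs already collected. No device interrogation needs to be added; the article describes none.

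The cost is a change of wording and slightly more analysis work, with no new patients, visits or procedures. The price is a weaker safety statement, but one that 40 patients can support. If a formal no-increase claim is wanted instead, it needs a justified margin and a sample size to match, which in most of the scenarios above is well beyond 20 per arm.

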## Methods/design

The study population will be a total of 40 patients with established CAD and left ventricular systolic dysfunction with an EF of ≤40% and HF in the NYHA class 3. CAD will be demonstrated based on previous coronary angiography (myocardial infarction > 6 months, presence of significant coronary stenosis, previosu revascularisation) or Tc SPECT (perfusion defects). The patient follow-up duration will be 12 months.

Patients have been on standard HF therapy for 3 months and in a stabilised state for at least 1 month, before enrolling in the clinical study. A list of inclusion and exclusion criteria is provided in Table 1.

**Table 1 Tab1:** Inclusion and exclusion criteria

Inclusion criteria:	
• Patients with chronic heart failure and left ventricular ejection fraction ≤40% with coronary artery disease and with symptoms of heart failure in the NYHA class 3 on standard heart failure therapy for 3 months and in a stabilised state for at least 1 month,	
• Age 40–80 years	
• Informed, written consent by the patient	
• Ability to comply fully with the study protocol	
• Negative pregnancy test (and effective contraception) in women with childbearing potential	
Exclusion criteria:	
• Previous bone marrow disease (especially myelodysplastic syndrome or non-Hodgkin’s lymphoma)	
• Repeated acute coronary syndrome <1 month	
• CRT device with LV lead in CS	
• Active infection or ATB treatment <1 week	
• Previous malignant ventricular arrhythmias without ICD implantation	
• Anemia (HTC ≤ 28%), leukocytosis (≥14.000/mm^3^) or thrombocytopenia (≤50.000/mm^3^)	
• Previous bleeding diathesis	
• Need for hematopoietic growth factor treatment (e.g. erythropoetin, G-CSF)	
• Impossibility of aspiration 240 ml of bone marrow	
• Hepathopathy or cirrhosis (bilirubin, ALT or AST ≥2,5x ULN)	
• Chronic kidney disease >3b stage (eGFR <45 ml/min/1.73m^2^)	
• Uncontrolled hypertension	
• Need for high dose (> 7.5 mg/day) corticotherapy within the next 6 months	
• Inability to stop anticoagulation therapy (> 72 h) before bone marrow aspiration	
• Known malignancies requiring actino or chemotherapy, or previous actinotherapy	
• Patients with a BMI > 40	
• Known allergy to contrast agents	
• Other comorbidities with a life expectancy of 6 months	

Patients will be randomised 1:1 to one of the following treatment methods: either retrograde BMAC administration via coronary sinus or the control group with standard HF therapy. Patients randomised to the control group will not undergo bone marrow collection, due to ethical reasons. Only standard right heart catheterisation will be performed as sham procedure.

The primary objectives of the clinical study are to improve the LV EF and reduce the LVESd/EDd and LVESV/EDV assessed by magnetic resonance imaging (MRI), and to improve exercise tolerance in the six-minute corridor walk test.

The secondary objectives include identifying the occurrence of severe ventricular arrhythmias according to 24-h ECG Holter monitoring, improving on the NYHA and CCS classes, reducing hospitalisations due to decompenzation of HF, assessing the impact on QoL of patients using the Kanas City Cardiomyopathy Questionare (KCCQ-12) and ensuring the safety of BMAC retrograde administration via coronary sinus by evaluating all adverse events (AE).

All patients will continue on the standard HF treatment during the clinical follow-up (ACE inhibitor/ATII blockers, beta-blockers, MRA, diuretics) and medication necessary for secondary CAD prevention (ASA/clopidogrel, statins). The monitored parameters will be measured echocardiographically in ICD-implanted patients not able to undergo MRI. Patient with cardiac resynchronization therapy (CRT) device (or CRT-ICD) with LV lead placed in CS will not be included. We also not include patients with known contrast allergy.

Written informed consent was obtained from each patient before enrollment in the study. The study protocol complied with the Declaration of Helsinki and was approved by the Ethics Committee of University Hospital Ostrava, Czech Republic. The study was registered at ClinicalTrials.gov (https://clinicaltrials.gov; NCT03372954).

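### The abstract names five primary endpoints and Methods six, but the stated 5% error and 80% power belong to the LVESV test alone

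*Protocol article*

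**What the plan says.** **Abstract, Methods/design paragraph.** Five measures carry the primary label: "The primary end-points (left ventricular end-systolic and end-diastolic diameters [LVESd/EDd] and volumes [LVESV/EDV] and left ventricular ejection fraction [LV EF". The walk test is not among them.

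**Methods/design section.** The same five measures come first: "The primary objectives of the clinical study are to improve the LV EF and reduce the LVESd/EDd". The sentence then continues "and LVESV/EDV assessed by magnetic resonance imaging (MRI), and to improve exercise tolerance in the six-minute corridor walk test", which makes the walk a sixth primary objective. The secondary objectives follow in a separate paragraph, and the walk is not there.

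**Sample size and statistical analysis.** The calculation uses one variable, "the difference of 13.0 + 12.9 ml in LVESV between study and control groups", with a 5% type I error and 80% power, and arrives at 17 per group and 40 in total after an allowance for loss. The analysis paragraph then sets a single threshold for all comparisons: p "< 0.05 will be considered significant".

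**Table 2 and Further follow-up.** The LV measures are taken at Visit 1 and month 12. The walk is taken at Visit 1, month 6 and month 12.

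**The concern.** Two things in the article do not fit together.

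First, the walk test is primary in Methods and absent from the primary list in the abstract. A reader cannot tell whether the trial has five or six primary endpoints, and the walk could be counted in or out once results are known.

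Second, the trial is sized on one of these endpoints, while the article labels five or six as primary and applies the same unadjusted threshold to each. Read as written, a claim of benefit on a primary endpoint could rest on any of five or six tests. The quoted error rate and power then no longer describe the trial's main conclusion. Which of the two figures fails depends on how the endpoints are combined into a verdict, and the article does not say.

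**Working it through.** **1. Reproduce the plan's own figure.** Inputs from the sample size section: difference 13.0 ml; 12.9 ml, taken as the standard deviation; error 5%, taken as two-sided because the article does not say; power 80%.

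- Standardised effect: 13.0 / 12.9 = 1.008.
- Normal approximation: n = 2 × (1.960 + 0.842)² / 1.008² = 15.5, so 16 per group.
- Exact two-sided t test: n = 16.5, so **17 per group, as stated**. A one-sided 5% test would give 13, so the two-sided reading is the one that matches.
- Loss of 10%: 17 / 0.9 = 18.9, so 19 per arm and 38 in total. The stated 40 rounds this up slightly.
- Power for LVESV with 17 evaluable per arm: 81%.

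The calculation is sound, and it is a calculation for LVESV only.

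**2. False-positive rate if any one primary endpoint suffices.** With k independent tests at 0.05 the rate is 1 − 0.95^k:

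- k = 5: 1 − 0.774 = 22.6%
- k = 6: 1 − 0.735 = 26.5%

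These are upper figures, not estimates. EF is computed from the two volumes, and diameters track volumes. The article gives no correlations, so the range below is assumed: 0.5 to 0.9 among the five LV measures, and 0.2 to 0.3 between each of them and the walk. Simulated two-sided t tests with 17 per arm and no treatment effect give approximately:

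| Correlation among LV measures | Any of five | Any of six |
|---|---|---|
| 0.5 | 18% | 22% |
| 0.7 | 15% | 19% |
| 0.9 | 10% | 14% |

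**3. Error and power if all primary endpoints must succeed.** With no effect on any endpoint, all tests reach significance together in less than 2% of trials at every correlation tried. In general, the chance of a false all-endpoint claim cannot exceed the 5% level of any single null test in the set. The error rate is therefore held.

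Power is not. The article gives no planning effect for the other endpoints, so each is assumed to have LVESV's standardised effect of 1.008 (81% power each at 17 per arm). Over the same correlation range, joint power is:

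- all five: about 52% (correlation 0.5) to 70% (0.9)
- all six: about 45% to 60%

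Both are below the stated 80%.

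**4. Cost of keeping every endpoint primary under an any-one rule.** Bonferroni would set the level at 0.05 / 5 = 0.010 or 0.05 / 6 = 0.0083. LVESV power with 17 per arm would fall from 81% to 58% or 56%. Restoring 80% needs 25 or 26 evaluable per arm, which is 28 or 29 after 10% loss, or 56 or 58 patients in total.

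**The case against.** The strongest case on the other side has four parts.

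*The 5% is correct for what it describes.* It appears in the LVESV calculation, and that test does have 5% error and about 80% power. The article makes no familywise claim, and the later threshold can be read as an ordinary per-test convention. This stands. A reader might infer that the 5% simply fails, but that follows only if any one endpoint is enough. If all must succeed, the error rate holds and it is the power that falls short.

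*Testing rules usually sit elsewhere.* A success rule, a testing order and the analysis time point for the walk may be in the full protocol or the analysis plan, neither of which is shown. This also stands, and their absence from a condensed article is not part of the point. It does not remove the disagreement between abstract and Methods, or the fact that the article labels five or six endpoints primary, sizes the trial on one and applies one flat threshold to all.

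*The Aim is not a third conflicting list.* It is tempting to read it as one, because the walk appears there in a sentence beginning "Furthermore, it will be associated with improved exercise tolerance in the six-minute corridor walk test, a decrease in NYHA and CCS classes", beside outcomes that Methods makes secondary. But the Aim states hypotheses and labels nothing primary or secondary. The conflict is between the abstract and Methods only.

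*The LV measures are strongly related.* This is correct, and it rules out the independent figures as headlines, including a joint power of 0.8^6 = 26%. Even at a correlation of 0.9, though, the any-one rate for five endpoints is about 10%, twice the nominal level.

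**Conclusion.** The point holds in a conditional form. The abstract and Methods disagree on whether the six-minute walk is primary, and the stated 5% and 80% describe the LVESV test, not a trial with five or six primary endpoints.

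Under an any-one rule the false-positive rate is roughly two to four times 5%. Under an all-must-succeed rule the error rate holds and joint power falls by about 10 to 35 percentage points from the stated 80%. The ranges rest on assumed correlations, on 17 evaluable patients per arm and, for joint power, on giving every endpoint LVESV's standardised effect.

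The documents do not support the stronger statements that the trial's error rate is 26%, or that no rule for success exists anywhere.

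**What to change.** Name LVESV at month 12 as the single primary endpoint, tested at two-sided 5%. It is the endpoint the sample size was built on, so the calculation and N = 40 stand unchanged.

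Make LV EF, LVEDV, LVESd, LVEDd and the six-minute walk at month 12 secondary. Either test them in a fixed order after LVESV, or report them as estimates with 95% confidence intervals and no confirmatory claim. Use the same list in the abstract and in Methods.

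The cost is the loss of primary claims on EF, LVEDV, diameters and walk distance. Because the article reports the trial as registered and consent as already obtained, the change also needs an amendment to the protocol and the registration. If the sponsor prefers another lead endpoint, such as LV EF, which both the Aim and Methods mention first, the sample size would have to be justified again for that endpoint.
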